### Study objectives

The objectives of the MATCH study were to identify the natural history of AVMs in the Asian population; to investigate the traditional and emerging angioarchitecture, hemodynamic, genetic, and environmental risk factors associated with AVM rupture; and to explore the superiority of the multidisciplinary assessment in improving the long-term outcomes. Based on this, individualized rupture and prognostic prediction models will be established to promote the precision medicine.

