### Clinical management

Conservation, microsurgery, embolization, SRS, and multimodal strategies are all included in this study. Patients will be divided into experimental and control groups according to whether the treatment protocols were formulated by a multidisciplinary team. In order to reduce workload, the MATCH Research Organizing Committee developed a standardized treatment protocol of multidisciplinary assessment as follows:

Ruptured AVMs: (1) microsurgery: microsurgery is recommended for AVMs not located in deep critical eloquent areas (brainstem, thalamus, basal ganglia, etc.) or more than 5 mm away from functional fiber bundles, regardless of the SM grade; (2) embolization: embolization should be performed 2–6 weeks after rupture; target embolization for hemorrhagic predictors could be considered as a monotherapy; palliative embolization can be used as an adjunctive strategy to reduce blood flow or nidus volume before microsurgery or stereotactic SRS; (3) SRS: SRS is indicated for patients with a nidus volume < 10 ml and not in the acute phase of hematoma (< 3 months); volume-stage or dose-stage can be used for giant AVMs. (4) Multimodality: the multimodality strategy such as single-stage combined embolization + resection (hybrid surgery) or staged embolization + resection or adjunctive embolization + resection/SRS or adjuvant SRS + resection are indicated for complex AVMs, such as giant AVMs involving deep eloquent areas, or AVMs with complex blood supply. (5) Conservation: conservation can be used for AVMs that are prone to severe disability due to intervention.

Unruptured AVMs: interventions are recommended if unruptured AVMs are assessed as being at high rupture risk or having refractory epilepsy or acceptable postoperative neurological deficits; otherwise, conservative treatment is recommended. The rupture risk stratification will be assessed qualitatively and quantitatively by the multidisciplinary team based on their own experience and the rupture prediction model to facilitate the division of the experimental and control groups. Regular multidisciplinary discussion meetings and fixed multidisciplinary groupings will ensure consistency of analytical results. Besides, the choice of intervention is the same as for ruptured AVMs.

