### Statistical analysis

Categorical variables were presented as percentages and continuous variables as mean with standard deviation (SD) or median with interquartile range (IQR). In univariable analyses, *t* test or Mann–Whitney test will be used to compare continuous variables, whereas *χ*2 test or Fisher’s exact test will be used to compare the categorical variables. Multivariable logistic regression will be used to evaluate the predictors of hemorrhage and long-term neurological outcomes in the cross-sectional dataset, and ORs with their 95% CIs will be evaluated. Univariable and multivariable Cox proportional hazard regression model or competing risk analysis or NCC will be performed to explore the predictors of subsequent hemorrhage in the survival dataset, and HRs with their 95% CIs will be evaluated. Kaplan–Meier plots of time-to-event outcomes of subsequent hemorrhage or complete obliteration (for AVMs who underwent SRS) among different treatment modalities will be presented. Generalized linear models or generalized linear mixed models will be used to explore potential correlates for continuous dependent prognostic parameters. Receiver operating curves (ROCs) will be used to assess the predictive validity in constructing predictive models for subsequent hemorrhage or long-term neurological outcomes. In cohort studies, propensity score matching (PSM) and inverse probability of treatment weighted (IPTW) will be used to adjust for confounding factors. Statistical significance was set at *p* < 0.05 (two-sided).

In this article, we compared the baseline demographic, clinical, and angioarchitecture characteristics of the multi-disciplinary and single-disciplinary assessment groups. Besides, although quality control has been maximized through the EDC system, there are still some missing values (less than 2%), which we have also reported. Proportions were used to describe the categorical variables, and means with SD or median with the IQR were used for continuous variables. Statistical analysis was performed using SPSS (version 25.0, IBM, New York, USA).

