Three AVM-related registration trials are cited in PubMed and recruiting currently. The first study, the Treatment of Brain AVMs (TOBAS), started recruiting in 2015 [25]. The general objective is to offer a care trial context for the management of ruptured and unruptured AVMs. In 2017, the TOBAS research team reported encouraging single-center recruitment rates and 61 patients were enrolled in the registry study [26]. The second study, the Multicenter AVM Research Study (MARS) study, an international observational cohort study, concentrated on the long-term outcomes and hemorrhagic predictors in unruptured AVMs [27]. In 2014, the MARS investigators reported that hemorrhagic presentation and increasing age were independent predictors of AVM rupture. It should be noted that MARS will perform causal analysis between the randomized data (ARUBA) and observational data (MARS). The third study, the New ASSessment of cerebral Arteriovenous Malformation yet Unruptured (NASSAU) study, a retrospective study comprising multicenter data from 1351 ARUBA-eligible patients who underwent Gamma Knife Surgery (GKS) [28]. They suggested that the period to break even for morbidity and mortality of AVMs treated with GKS compared to untreated patients in ARUBA was found to be 5 years. The NASSAU is a well-conceived study and reveals the severe limitations of ARUBA.

Exception for the TOBAS study, most of the aforementioned registry studies only focus on unruptured AVMs, and the current disclosed data in the TOBAS study are not encouraging in terms of the recruitment of participating centers and patients. Besides, the optimal intervention strategy for ruptured AVMs remains elusive, especially in patients with similar interventional indications or complex angioarchitecture. The MATCH study can better address this gap as the nationwide prospective registry that can provide adequate samples for prognostic analysis of each treatment strategy and can support the establishment of the prognostic prediction model. Of course, the MATCH study will also explore optimal treatment strategies for unruptured AVMs and develop predictive models that can accurately predict long-term outcomes, and compare the predictive performance with previous models [29].

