Another strength of the MATCH study was that novel hemodynamic parameter are introduced and will be used to create rupture prediction models with better predictive performance than previous models [4]. The characteristic angioarchitecture is caused by specific hemodynamics. Color-coded DSA is a breakthrough research direction in recent years for AVM hemodynamic studies [16, 17, 30], and the MATCH study will explore it in depth. The MATCH study will use the NCC study to explore and validate hemorrhagic predictors and build rupture prediction models based on this, which is expected to provide precise prediction of future cerebrovascular events in AVMs. Besides, the MATCH study will explore the superiority of multidisciplinary comprehensive assessment, promote the formulation of individualized treatment protocols conducted by multidisciplinary teams, and effectively promote precision medicine.

There are several limitations of MATCH. First, despite being represented as a whole, potential selection bias of patients was unavoidable since the selected neurosurgical center in this study mostly represented the hospitals with more medical resources and expertise than the low-level hospitals. Second, the MATCH study did not involve the uniform collection and analysis of biological samples from multiple centers due to research funding constraints. Third, the Multidisciplinary Professional Committee of MATCH developed the multidisciplinary standardized treatment protocol to reduce workload. However, the protocol contains overlapping indications between different treatment strategies, which would lead to the deviation of grouping. The multidisciplinary team will decide whether to classify them as experimental or control groups at the regular meetings. Finally, the experimental group has significant less samples than the control group, but with the integration and promotion of the multidisciplinary model, the difference in sample size will be eliminated.

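### ROC curves are the only stated test of predictive validity, but they cannot support the promised precise and accurate prediction or reveal uncorrected nested case-control sampling

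*Protocol article*

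**What the plan says.** The Statistical analysis section of the protocol article gives one criterion for both families of models: "Receiver operating curves (ROCs) will be used to assess the predictive validity in constructing predictive models for subsequent hemorrhage", with the models for long-term neurological outcome named in the same sentence. Nowhere does the article mention calibration, observed against expected risk, or an overall accuracy score.

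What the models are meant to deliver is stated elsewhere:

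- Study objectives: "individualized rupture and prognostic prediction models will be established to promote the precision medicine".
- Discussion, on the rupture model: "which is expected to provide precise prediction of future cerebrovascular events in AVMs".
- Discussion, on the outcome models: the study will "develop predictive models that can accurately predict long-term outcomes" and compare their performance with earlier models. No measure is given for that comparison.

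Study design and Discussion both say that the rupture model will come from nested case-control studies within the registry. The ratio of controls to cases is not given.

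**The concern.** The criterion and the promise do not match. A ROC curve uses only the order of the predicted risks. Any strictly increasing transformation of them leaves the curve and its area unchanged. A model that puts every patient's risk far too high or too low therefore gets the same ROC curve as a correct one. An individualized prediction that is called precise or accurate is a statement about the risk itself, and ROC cannot test that.

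The design makes this more than a theoretical gap. Case-control sampling raises the proportion of events in the analysed data well above that in the cohort. Unless this is corrected, the model's absolute risks are wrong by construction, and the stated criterion would not show it. At stake is whether the published models could be described as accurate on evidence that cannot bear on accuracy.

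**Working it through.** The article states no AUC target, calibration figure or sample size for the models, so there is no figure of its own to reproduce. The check has two parts.

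**1. What ROC can see.** The area under the curve is the probability that a randomly chosen patient with the event has a higher predicted risk than one without it. It depends on ranks alone. Adding a constant to the log-odds, or multiplying the log-odds by a positive constant, leaves it unchanged. This needs no assumption about the data.

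**2. What uncorrected case-control sampling does to absolute risk.**

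Inputs:

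- Annual rupture risk *a* of 1% to 3% if untreated (Background).
- Horizon of 3 years (Outcomes measurements).
- Assumed: one standard normal predictor with a log-odds slope of 1, all cases sampled, and *k* = 1 or 4 controls per case.
- Simplification: controls are drawn once from those without the event, not matched on time at risk as in a true nested case-control study.

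Three-year risk is p = 1 − (1 − a)³:

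- a = 1%: 1 − 0.99³ = 2.97%
- a = 2%: 1 − 0.98³ = 5.88%
- a = 3%: 1 − 0.97³ = 8.73%

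If all cases and a fraction k·p/(1 − p) of non-cases are sampled, an uncorrected logistic model multiplies every patient's odds by (1 − p)/(k·p):

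- a = 1%: 0.9703/0.0297 = 32.7 for k = 1, and 8.2 for k = 4
- a = 2%: 0.9412/0.0588 = 16.0 for k = 1, and 4.0 for k = 4
- a = 3%: 0.9127/0.0873 = 10.5 for k = 1, and 2.6 for k = 4

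In a simulated cohort of 1,000,000 patients, the model was fitted to the sampled data and then applied to the whole cohort:

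| Annual risk | Observed 3-year risk | k | Mean predicted risk | Predicted/observed | AUC, correct model | AUC, uncorrected model |
|---|---|---|---|---|---|---|
| 1% | 2.98% | 1 | 40.8% | 13.7 | 0.754 | 0.754 |
| 1% | 2.98% | 4 | 17.5% | 5.9 | 0.754 | 0.754 |
| 2% | 5.88% | 1 | 41.5% | 7.1 | 0.753 | 0.753 |
| 2% | 5.88% | 4 | 18.0% | 3.1 | 0.753 | 0.753 |
| 3% | 8.77% | 1 | 42.1% | 4.8 | 0.752 | 0.752 |
| 3% | 8.77% | 4 | 18.4% | 2.1 | 0.752 | 0.752 |

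An error in the other direction is equally invisible. Doubling the linear predictor at 2% per year gives a mean prediction of 1.0% against 5.9%, again with an AUC of 0.753.

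A time-matched nested case-control analysis that reports only hazard ratios, as the section on Statistical analysis allows, gives no absolute risk until a baseline risk from the full cohort is added. The conclusion is the same: the step that produces the absolute risk is one that ROC does not check.

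**The case against.** The strongest reply is that this is only an omission. The sentence does not say that ROC is the sole measure, ROC is a proper measure of discrimination, and a fuller protocol or analysis plan could add calibration. That is fair, and "only" here means the only measure stated in this article. What remains is that the article does not leave the criterion open. It names ROC as the assessment of predictive validity and publishes claims of precision and accuracy beside it.

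A second reply is that those claims are expectations in the Discussion and that no pass mark is set. This also stands in part: the article contains no formal gate that a poor model would pass. The claims are still about agreement with actual risk, and the stated criterion cannot bear them out.

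A third reply is that a logistic model with an intercept reproduces the mean risk of its own development data. That is true, but with case-control data it is the mean of the sample, not of the cohort.

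A reader might go further and infer that a model passed on ROC alone will move a known share of patients across a high-risk line. Clinical management says that rupture risk is "assessed qualitatively and quantitatively by the multidisciplinary team based on their own experience and the rupture prediction model" and that "interventions are recommended if unruptured AVMs are assessed as being at high rupture risk". The documents do not support that inference:

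- They do not say which model is meant. The multidisciplinary team dates from June 2018 and 500 patients had been assessed by April 2021, whereas the registry's models are still to be established, and the Background already refers to an existing prediction model.
- The model is one input beside the team's experience.
- No absolute-risk line is given. A cut set on the score's own scale would label the same patients after any rescaling.

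For that reason no share of patients above a cut-off is reported here.

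**Conclusion.** The point holds in a limited form. The one stated criterion measures ranking. It cannot support the promised individualized, precise and accurate prediction, and it cannot detect distorted absolute risk if a model built from nested case-control data is not corrected for sampling.

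That ROC is unchanged by such distortion is exact. Its possible size is illustrative: mean predicted risk 2.1 to 13.7 times the observed risk over 1% to 3% per year and one or four controls per case. Those figures rest on the assumed slope, the assumed ratios, simplified sampling and no correction at all. The article does not say that the sampling will go uncorrected. The primary outcome, mRS at 3 years, and the comparison of multidisciplinary with single-disciplinary assessment are not affected. The change is worth making before the models are reported.

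**What to change.** Extend the ROC sentence in Statistical analysis along these lines:

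*Predictive validity will be assessed by discrimination (ROC) and by calibration at 3 years: observed against predicted risk, calibration slope and a calibration plot. Observed hemorrhage risk will be taken from the cumulative incidence, and observed mRS outcome from the proportion at 3 years. Models built from nested case-control data will use sampling weights or the baseline risk of the full cohort, and their calibration will be checked against the full cohort. Models will be described as accurate only where calibration is adequate.*

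The two outcomes need different estimates of observed risk because hemorrhage is a time-to-event outcome while mRS is a status at a fixed time. The change uses data that the registry already collects and sets no clinical threshold. Its cost is a little more analysis, and reported model performance may look less favourable.

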## Results

Patient recruitment is still ongoing, and we now summarize the data in stages as follows: Between August 2011 and April 2021, 3653 brain AVM patients were consented and registered to the MATCH study in 11 participating sites. After rigorous screening, a total of 412 patients were excluded. Finally, a total of 3241 AVMs fulfilled the initial inclusion criteria. Among them, 15.43% (500 AVMs) underwent multidisciplinary assessment and received standardized treatment as prescribed by MATCH. The detailed patient enrollment flow chart is shown in Fig. 2. The included patients had similar baseline demographic, clinical, and imaging characteristics as those excluded (Table 2).

**Fig. 2 Fig2:**
[figure not shown]
Flow chart of patients’ enrollment in MATCH. AVM, arteriovenous malformation; MATCH, registry of multimodality treatment for brain arteriovenous malformation in mainland China; SRS, stereotactic radiosurgery

**Table 2 Tab2:** Baseline characteristics of included and excluded AVMs in the MATCH study

Characteristics	Included	Excluded	*P* value
Baseline demographic data	*N* = 3241	*N* = 412	
Sex, male, n (%)	1911 (59.0)	240 (58.3)	0.782
Age (years)			
Mean ± SD	28.4 ± 14.6	28.3 ± 12.2	0.831
Baseline clinical data^a^	*N* = 3241	*N* = 371	
Onset manifestation			
Hemorrhage, n (%)	1984 (61.2)	226 (60.9)	0.911
Seizure, n (%)	754 (23.3)	84 (22.6)	0.858
Admission mRS			
Median, IQR	1 (1, 2)	1 (0, 2)	0.788
Baseline imaging data^b^	*N* = 3241	*N* = 316	
Location, supratentorial, n (%)	2844 (87.7)	281 (88.9)	0.542
AVM maximum diameter (cm)			
Mean ± SD	3.4 ± 1.9	3.3 ± 2.0	0.857
Eloquence, n (%)	1794 (55.3)	180 (56.9)	0.583
Deep venous drainage, n (%)	1284 (39.6)	122 (38.6)	0.726
Spetzler-Martin Grade			0.848
I-III	2694 (83.1)	264 (83.5)	
IV-V	547 (16.9)	52 (16.5)	

*AVM* Arteriovenous Malformation, *IQR* Interquartile Range, *N* Denominator, *n* numerator, *MATCH* Registry of Multimodality treatment for brain ArTeriovenous malformation in mainland China, *mRS* Modified Rankin Scale, *SD* Standard Deviation

^a^ 41 AVMs in the excluded cohort missing critical baseline clinical data

^b^ 96 AVMs in the excluded cohort missing critical baseline imaging data

Baseline demographic and clinical characteristics of the included AVMs are presented in Table 3. Overall, 59.0% were male, and the average age was 28.4 years. Among all enrolled patients, 61.2% (1984 cases) had rupture history, and 2268 rupture events occurred before admission. The median duration from diagnosis to treatment (including intervention and conservation) was 2.9 months. Microsurgery is the dominant treatment strategy (35.7%), 12.7% received endovascular embolization as monotherapy, and 14.8% underwent SRS. Staged embolization + SRS is the most common multimodal treatment strategy (11.8%). At the most recent follow-up, 7.8% were lost. The median follow-up duration was 5.6 years, and 79.4% have completed 3 years of follow-up. There were no statistically significant differences in all demographic and clinical characteristics between single-discipline and multidiscipline cohorts except for the follow-up duration.

**Table 3 Tab3:** Baseline demographic and clinical characteristics of the participants in the MATCH study

Characteristics	All patients	Single-disciplinary cohort (2011.08–2021.04)	Multidisciplinary cohort (2018.06–2021.04)	*P* value
No. of patients	*N* = 3241	*N* = 2741	*N* = 500	
Ethnicity, male, n (%)	1911 (59.0)	1624 (59.2)	287 (57.4)	0.440
Age (years), mean ± SD	28.4 ± 14.6	28.3 ± 14.4	29.4 ± 15.6	0.118
Race, Han, n (%)	3109 (95.9)	2629 (95.9)	480 (96.0)	0.929
Onset manifestation				
Hemorrhage, n (%)	1984 (61.2)	1677 (61.1)	307 (61.4)	0.927
Seizure, n (%)	754 (23.3)	647 (23.6)	107 (21.4)	0.283
Headache, n (%)	698 (21.5)	587 (21.4)	111 (22.2)	0.695
Neurofunctional deficit, n (%)	583 (18.0)	488 (17.8)	95 (19.0)	0.522
Others, n (%)	271 (8.4)	230 (8.4)	42 (8.4)	0.995
Frequency of hemorrhage before admission, n	2268	1917	351	0.906
Type of seizure, generalized, n (%)	629 (19.3)	542 (19.7)	87 (17.4)	0.217
Duration from diagnosis to treatment (months), median, IQR	2.9 (0.9, 12.8)	2.8 (0.9, 12.9)	3.0 (0.9, 12.6)	0.471
Admission mRS, median, IQR	1 (1, 2)	1 (1, 2)	1 (1, 2)	0.653
Type of treatment				
Conservation, n (%)	491 (15.1)	412 (15.0)	79 (15.8)	0.659
Microsurgery, n (%)	1158 (35.7)	991 (36.2)	167 (33.4)	0.237
Embolization, n (%)	412 (12.7)	346 (12.6)	66 (13.2)	0.722
SRS, n (%)	480 (14.8)	413 (15.1)	67 (13.4)	0.334
Hybrid surgery, n (%)	141 (4.4)	120 (4.4)	21 (4.2)	0.858
Staged embolization + Microsurgery, n (%)	83 (2.6)	67 (2.4)	16 (3.2)	0.325
Embolization + SRS, n (%)	381 (11.8)	312 (11.4)	69 (13.8)	0.123
Microsurgery + SRS, n (%)	45 (1.4)	39 (1.4)	6 (1.2)	0.695
Microsurgery + Embolization + SRS, n (%)	50 (1.5)	41 (1.5)	9 (1.8)	0.612
Follow-up duration (years), median, IQR	5.6 (3.4, 7.9)	6.3 (4.4, 8.3)	2.4 (1.8, 3.3)	< 0.001^*^
Lost follow-up, n (%)	253 (7.8)	204 (7.4)	49 (9.8)	0.071
Patients who have completed 3 years follow-up, n (%)	2372 (79.4)	2181 (86.0)	191 (42.4)	< 0.001^*^

*IQR* Interquartile Range, *N* Denominator, *n* numerator, *MATCH* Registry of Multimodality treatment for brain ArTeriovenous malformation in mainland China, *mRS* Modified Rankin Scale, *SD* Standard Deviation, *SRS* Stereotactic Radiosurgery

^*^Statistical significance (*p* < 0.05)

Baseline imaging characteristics of the included AVMs are presented in Table 4. Among them, 87.8% were supratentorial, and the median maximum diameter was 2.9 cm, 55.4% involved eloquent area. Due to poor image quality or absence of requisite sequences, the imaging characteristic data of some patients were missing (less than 2%). Overall, the median Spetzler-Martin and Lawton-Young grades were 3 and 5, respectively. There were no statistically significant differences in imaging characteristics between single-discipline and multidiscipline cohorts.

**Table 4 Tab4:** Baseline imaging characteristics of the participants in the MATCH study

Characteristics	All patients	Single-disciplinary cohort (2011.08–2021.04)	Multidisciplinary cohort (2018.06–2021.04)	*P* value
No. of patients	*N* = 3241	*N* = 2741	*N* = 500	
Location, supratentorial, n (%)	2844 (87.8)	2417 (88.2)	427 (85.4)	0.081
Maximum diameter (cm), median, IQR	2.9 (2.0, 4.3)	2.9 (2.0, 4.3)	3.0 (2.1, 4.3)	0.468
Eloquence, n (%)				0.149
Yes	1794 (55.4)	1532 (55.9)	262 (52.4)	
No	1447 (44.6)	1209 (44.1)	238 (47.6)	
Feeding artery dilation, n (%)				0.526
Yes	1499 (46.3)	1275 (46.9)	224 (45.3)	
No	1714 (52.9)	1444 (53.1)	270 (54.7)	
Missing	28 (0.9)	22 (0.8)	6 (1.2)	
No. of feeding artery, median, IQR	2 (1, 3)	2 (1, 3)	2 (1, 3)	0.547
Missing	29 (0.9)	22 (0.8)	7 (1.4)	
Watershed AVM, n (%)				0.984
Yes	886 (27.3)	749 (27.5)	137 (27.5)	
No	2339 (72.2)	1978 (72.5)	361 (72.5)	
Missing	16 (0.5)	14 (0.5)	2 (0.4)	
Flow-related aneurysm, n (%)				0.830
Yes	539 (16.6)	458 (16.9)	81 (16.5)	
No	2670 (82.4)	2259 (83.1)	411 (83.5)	
Missing	32 (1.0)	24 (0.9)	8 (1.6)	
Diffuse nidus, n (%)				0.755
Yes	1158 (35.7)	975 (35.9)	183 (36.6)	
No	2060 (63.6)	1743 (64.1)	317 (63.4)	
Missing	23 (0.7)	23 (0.8)	0 (0.0)	
Deep venous drainage, n (%)				0.159
Yes	1258 (38.8)	1078 (39.6)	180 (36.3)	
No	1957 (60.4)	1641 (60.4)	316 (63.7)	
Missing	26 (0.8)	22 (0.8)	4 (0.8)	
No. of draining vein, median, IQR	1 (1, 2)	1 (1, 2)	1 (1, 2)	0.103
Missing	29 (0.9)	22 (0.8)	7 (1.4)	
Drainage vein stenosis, n (%)				0.622
Yes	506 (15.6)	432 (15.9)	74 (15.0)	
No	2706 (83.5)	2287 (84.1)	419 (85.0)	
Missing	29 (0.9)	22 (0.8)	7 (1.4)	
Venous pouches, n (%)				0.560
Yes	506 (15.6)	424 (15.6)	82 (16.6)	
No	2706 (83.5)	2295 (84.4)	411 (83.4)	
Missing	29 (0.9)	22 (0.8)	7 (1.4)	
Spetzler-Martin Grade, median, IQR	3 (2, 3)	3 (2, 3)	3 (2, 3)	0.348
Missing	26 (0.8)	22 (0.8)	4 (0.8)	
Lawton-Young Grade, median, IQR	5 (4, 6)	5 (4, 6)	5 (4, 6)	0.788
Missing	27 (0.8)	23 (0.8)	4 (0.8)	

*AVM* Arteriovenous Malformation, *IQR* Interquartile Range, *N* Denominator, *n* numerator, *MATCH* Registry of Multimodality treatment for brain ArTeriovenous malformation in mainland China, *mRS* Modified Rankin Scale, *SD* Standard Deviation

